### Detail of outcome measures collected

#### SOFA score (Additional file 3)

SOFA score will be registered until discharge from ICU.

#### Blood products and procoagulants

Timings, total number (and doses if appropriate) of different blood products and procoagulants administered both pre-hospital and after admission to the study centre, during resuscitation and after 6 and 24 h will be recorded including:RBC, fresh frozen plasma (FFP)/Octaplas, cryoprecipitate, platelets, whole blood and/or autologous RBC from cell salvageCoagulation factor concentrates (prothrombin complex concentrate (PCC), fibrinogen, activated recombinant factor VII (rFVIIa))TXA

#### Fluids

Timings (during first 24 h only) and total volume of different fluids administered both pre-hospital and after admission to the study centre until 24 h will be recorded including crystalloids, colloids and hypertonic saline.

#### Thromboprophylaxis/prothrombotic medication

Type of medication administered, timings, dose and indication will be recorded daily until day 28 with particular attention to duration of treatment (stop date).

#### Bleeding episodes

Qualifying episodes will be defined by radiological evidence, like contrast extravasation on CT scan, and/or clinical suspicion, like haemodynamic instability, combined with transfusion requirement after initial haemostasis (defined as the point 1 h from the last administration of RBC and the treating clinician believes primary haemostasis has been achieved).

#### Ventilator-free days

Calculated by the subtracting the number of days spent on mechanical ventilation from 28. Death before day 28, recorded as 28.

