### Secondary endpoints

The secondary endpoints listed below will be analysed in order to provide a sensitive and comprehensive description of outcomes and health care resource demands for the VHA and CCT arm subjects:All-cause mortality at 6 and 24 h and 28 and 90 days post admissionDuration and severity of coagulopathy until haemostasis, as defined by the area under the time multiplied by Prothrombin Ratio (PTr) curve, with coagulopathy defined as PTr > 1.2. Patients who die will have their time of haemostasis set at 24 h, and last PTr extrapolated to this time pointProportion of patients who have corrected coagulopathy, defined as PTr < 1.2, after first 8 units of RBCTime to haemostasis (defined as having occurred at the end of the first hour free of red cell transfusions and the treating clinicians believe primary haemostasis has been achieved)Time spent in coagulopathic condition, defined as PTr ≥ 1.2, until haemostasis, defined as the point 1 h from the last administration of RBC and the treating clinician believes that primary haemostasis has been achievedBlood products administered (RBC, plasma, platelets alone and in total) within first 6 and 24 h after admission28-day ventilator-free and ICU-free days (patients who die in hospital during the 28-day study period will be considered to have zero hospital-free days)Total hospital length of stay28-day symptomatic thromboembolic events defined as: deep venous thrombosis (DVT) diagnosed by compression ultrasound or venography, pulmonary embolism diagnosed by computed tomography (CT) pulmonary angiogram or ventilation-perfusion scan or myocardial infarction and/or stroke identified by standard clinical diagnostic investigation(s)Incidence of transfusion-related complicationsIncidence of organ dysfunction, defined by Sequential Organ Failure Assessment (SOFA) scoreHealth care resource, productivity costs and HRQoL (EuroQol EQ-5DTM at discharge or day 28, and at day 90)Lifetime health economic cost-effectiveness of personalised VHA-guided haemorrhagic treatment versus MTP-based on best practice and CCTs

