### Statistical considerations

#### Sample size

Based upon legacy registry data from the partners, approximately 28% of patients will need massive transfusion or die. It is expected that this figure will decrease to an overall proportion of 15% in the VHA group (i.e. using VHA-guided strategy). In order to detect a difference from 28% to 15% with a power of 80% and a two-sided alpha of 0.05, 170 patients per group are required. One hundred and ninety-six patients per study arm allows a 13% dropout rate, with an allocation ratio of 1. The planned sample size for this study is 392 patients for which MTP is activated and transfusions initiated, 196 in each study arm.

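### As written, the ventilator-free-days definition gives patients who die the most favourable score, which contradicts the zero rule attached to the same secondary endpoint

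*Protocol article*

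**What the plan says.** Two places in the protocol article bear on how a death is scored.

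- **Detail of outcome measures collected, Ventilator-free days.** The score is "Calculated by the subtracting the number of days spent on mechanical ventilation from 28". It therefore runs from 0 to 28 and higher is better. The next sentence is the death rule: "Death before day 28, recorded as 28".
- **Secondary endpoints.** Ventilator-free and ICU-free days over 28 days form one item. The parenthesis attached to that item reads: "patients who die in hospital during the 28-day study period will be considered to have zero hospital-free days". No endpoint called hospital-free days is listed; the next item is total length of hospital stay.

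The ICU days section defines an ICU day but gives neither a formula for ICU-free days nor a death rule. Duration of mechanical ventilation is part of the secondary objective, and ventilator-free days are among the outcomes named in the End of study definition.

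**The concern.** A free-days outcome combines survival and duration of support in one number. It works only if death takes the worst value. Under the literal definition death takes the best value, so each additional death raises the mean of its arm. The section on adverse event reporting describes a population at high risk of dying, so the rule would apply to many patients.

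The two places also differ in scope: one covers any death before day 28, the other only deaths in hospital. A programmer working from the outcome definition and one working from the endpoint list would produce different results, possibly of opposite sign. If the choice is left until the data are unblinded, it becomes a post hoc choice.

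**Working it through.** **Inputs.** The formula and the two death scores (28 and 0) come from the sections above. The article states neither 28-day mortality nor survivors' ventilator-free days, so both are assumed below. The rates in the Sample size section cannot stand in for mortality: "approximately 28% of patients will need massive transfusion or die" describes death or massive transfusion, and the endpoint it serves is assessed at 24 h. The article gives no planned figure for ventilator-free days, so there is none to reproduce.

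**One patient.** A survivor who is never ventilated scores 28 − 0 = 28. A patient who dies on day 1 scores 28 under the literal definition and 0 under the zero rule. Each death moves by 28 points between the rules.

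**Arm means.** Let m be 28-day mortality, S the survivors' mean score and c the score given to a death:

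mean = (1 − m) × S + m × c

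For arms A and B with the same S, the difference A − B is:

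- c = 28: (mA − mB) × (28 − S), which favours the arm with more deaths whenever S is below 28
- c = 0: −(mA − mB) × S, which penalises that arm
- gap between the two rules: 28 × (mA − mB), whatever S is. For 5 percentage points, 28 × 0.05 = 1.4 days.

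**Worked case** (assumed: S = 20 in both arms, mortality 25% with CCT and 15% with VHA):

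| Death scored | CCT | VHA | VHA − CCT |
|---|---|---|---|
| 28 | 0.25 × 28 + 0.75 × 20 = 22.0 | 0.15 × 28 + 0.85 × 20 = 21.2 | −0.8 |
| 0 | 0.75 × 20 = 15.0 | 0.85 × 20 = 17.0 | +2.0 |

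The swing is 2.0 + 0.8 = 2.8 days, which equals 28 × 0.10.

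**Range over S** (assumed mortality 30% against 20%; entries are the higher-mortality arm minus the other):

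| S | Death = 28 | Death = 0 |
|---|---|---|
| 14 | +1.4 | −1.4 |
| 18 | +1.0 | −1.8 |
| 22 | +0.6 | −2.2 |
| 26 | +0.2 | −2.6 |

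The sign reverses in every row, but the spurious advantage shrinks as S approaches 28.

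**When S differs between arms.** Take the worked case again with CCT at 22.0 under the literal rule. VHA reaches the same mean when 0.15 × 28 + 0.85 × S = 22.0, that is S = 17.8 / 0.85 = 20.9. If VHA survivors averaged about 0.9 day more than CCT survivors, the literal rule would show no difference; with a larger advantage, VHA would look better despite the bias.

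**The case against.** The strongest reply is that this is a wording slip and not a chosen analysis rule. The death sentence names no quantity, and the sentence before it speaks of days on the ventilator. If a death is recorded as 28 ventilator days, the score is 28 − 28 = 0, which agrees with the endpoint list. The parenthesis there can sensibly qualify only the item it follows, so it shows the intended direction. This is plausible, and a reader should not infer that the authors meant to reward death. But the sentence stands under a heading and a formula for ventilator-free days and does not say that it means ventilator days. On either account it has to be changed. Nor is this a detail left to an analysis plan: the article states a specific value, and a plan faithful to that value would carry the error forward.

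Two further objections stand and limit the point. First, a reader might infer that a survival benefit of VHA must appear as fewer ventilator-free days. That is certain only when survivors are ventilated equally in both arms; otherwise the rule is a bias in that direction, and the observed sign can go either way. Second, a reader might infer that early deaths also score near 28 ICU-free days. The article does not say so: it gives no formula for ICU-free days, and the only death rule attached to them is the zero in the endpoint list.

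It is also fair that this is one secondary endpoint among many, and that all-cause mortality is reported separately at 6 h, 24 h, 28 days and 90 days. A survival difference could not be hidden by this score.

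**Conclusion.** The point holds as a contradiction between two sections on a secondary endpoint, one of which is wrong as written. Taken literally, the ventilator-free-days section gives deaths the best score, against the zero rule in the endpoint list, and no other section resolves it. The gap between the rules is 28 days times the difference in 28-day mortality. The spurious advantage to the arm with more deaths is that mortality difference times (28 − S), for equal S. With an assumed 10-point difference it runs from 1.4 days at S = 14 to 0.2 days at S = 26. These sizes are illustrations, because the article gives neither mortality at 28 days nor survivors' ventilation. The primary endpoint, its analysis and the sample size do not depend on this rule.

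**What to change.** Make three edits so that one rule applies throughout:

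1. In the Ventilator-free days section, replace the death sentence with: *any death before day 28, in or out of hospital, counts as 0 ventilator-free days.*
2. In the parenthesis under Secondary endpoints, replace zero hospital-free days with *zero ventilator-free and zero ICU-free days*.
3. In the same parenthesis, remove the restriction to deaths in hospital, so that it covers any death within 28 days, and use the same day-28 boundary in both places.

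The cost is two sentences and the matching lines of the derivation program. No new data are needed. The article reports that recruitment was still under way, so the change can be made and dated before any unblinded analysis.

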#### Vasopressor days

Calculated as the total number of days spent on inotropic drugs, including for instance noradrenaline, dobutamine, vasopressin.

#### Renal replacement therapy days

Calculated as the number of days spent on haemodialysis or haemofiltration.

#### ICU days

The total length of stay in the ICU. If the patient is in the ICU at any time point during a calendar day, this day will be considered an ICU day.

#### Length of stay

Length of stay will be recorded in days, for the total number spent in ICU and in hospital. If the patient is in the hospital at any time point during a day, this day will be considered a hospital day.

#### Surgical episodes

Description, timing, duration and reasons for all surgical episodes will be recorded. This includes interventional radiology and bedside surgical interventions in addition to major surgical procedures.

#### Thromboembolic events

Symptomatic venous thromboembolic events will be recorded, as confirmed by either compression ultrasound/venography (DVT or by CT – pulmonary angiogram/ventilation – perfusion scan (pulmonary embolism (PE)). Other thromboembolic events, such as myocardial infarction and/or stroke, will be identified by standard clinical diagnostic investigations(s).

#### Patient disposition

First destination after discharge and disposition at 90 days post admission will be recorded as either home, rehabilitation facility, nursing home, other hospital or other.

#### Quality of life (Qol)

Subject quality of life will be assessed using the EuroQoL EQ-5D^™^ questionnaire, a standardised instrument for use as a measure of health outcome. Quality of life assessment will be conducted in the study centre upon discharge of the subject from hospital and at 90 days post admission.

The in-hospital (i.e. discharge) questionnaire will be conducted by research investigators with the patient where possible, but may also be completed with patient’s PC if necessary. The questionnaire can be completed in less than 5 min. Where the subject has already left hospital, the questionnaire will be posted out with a return stamped addressed envelope.

Patients who have not returned the questionnaire within 2 weeks of the initial request will be telephoned as a reminder to complete the questionnaire and may be asked to complete it over the telephone if necessary.

A further EuroQoL EQ-5D^TM^ questionnaire will be provided to assess subject quality of life at 90 ± 5 days post admission. Confirmation with the local (i.e. hospital care record system) and regional resources (i.e. NHS Health and Social Care Information Centre Spine Services) will ensure that only surviving patients receive a questionnaire.

### Cessation of study care (haemostasis)

For the purposes of this comparative study, haemostasis (end of study care) will be defined as the point 1 h from the last administration of RBC and the treating clinician believes that primary haemostasis has been achieved.

### Procedure for data collection

Study subject data will be captured locally using a paper Case Report Form (CRF), following local data security routines. CRF data are transferred and uploaded to a centralised study database whereupon study data integrity is reviewed weekly by the Trial Coordinating Centre.

### Adverse event reporting

Patients included in this trial have a high risk of morbidity and mortality, with either treatment being administered during a phase of critical bleeding and circulatory failure. Therefore, patients have a very high risk of experiencing several adverse events (AEs) and serious adverse events (SAEs). All SAEs, expected or not, will be recorded on a SAE form. Any SAE, death or thromboembolic or ischaemic events (myocardial infarction, stroke, pulmonary embolus, DVT) that are considered to be ‘related’ and unexpected are to be reported to the sponsor within 24 h, and to the Main Research Ethics Committee (MREC) within 15 days in line with the required timeframe.

### Urgent safety measures

The chief investigator (CI) will take urgent safety measures to ensure the safety and protection of the clinical trial subjects from any immediate hazard to their health and safety. The measures should be taken immediately. In this instance, the approval of the Ethics Committee prior to implementing these safety measures is not required. However, it is the responsibility of the CI to inform the sponsor and the Main Research Ethics Committee (MREC) (via telephone) of this event immediately.

The CI has an obligation to inform both the MREC in writing within 3 days, in the form of a substantial amendment. The sponsor (Joint Research Management Office (JRMO)) must be sent a copy of the correspondence with regards to this matter.

### Annual safety reporting

The CI will send the Annual Progress Report to the MREC using the NRES template (the anniversary date is the date on the MREC ‘favourable opinion’ letter from the MREC) and to the sponsor.

### Subject withdrawal

Every reasonable effort will be made to maintain protocol compliance and to retain patient participation in the study, consistent with the provisions of informed consent and good clinical practice. The following are potential reasons why a patient may be withdrawn from the study:Withdrawal of consent/agreementRetrospective exclusion: if a patient is deemed to not meet one or more of the inclusion/exclusion criteria in retrospect they will be withdrawn from the studyMajor protocol deviation from the study design by the subject, observed or suspected by the investigatorAdministrative: the sponsor or monitoring committees decide to terminate or discontinue the studyThe subject’s health would be jeopardised by continued participation and hence will be withdrawn at the discretion of the investigator

The study withdrawal form will be completed for these patients and a reason for withdrawal captured. All subject’s withdrawn from the study will be managed in accordance with the hospital’s standard procedures.

### Data collection and follow-up for withdrawn subjects

Patients who withdraw from the study after randomisation will be followed for safety by conducting safety assessments through to the end of day 28. If a patient who withdraws has an ongoing SAE every effort must be made to follow up such events until satisfactory resolution is obtained or until further follow-up is no longer warranted.

### Subject replacement

Subjects who withdraw from the study will be replaced.

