#### Method of analysis

All primary and secondary outcomes will be analysed as intention-to-treat, and will include all randomised patients for whom the primary outcome of ‘alive’ and ‘free of massive transfusion’ at 24 h is recorded. The primary endpoint of patients who are alive and free of massive transfusion at 24 h will be assessed by difference in proportion with 95% confidence intervals. The chi-square test or Fischer’s exact test will be used were appropriate. Absolute risk reduction and relative risk reduction by VHA-guided therapy will be calculated.

Kaplan-Meier mortality estimates between the two arms for all-cause mortality at 6 and 24 h, as well as 28 and 90 days post admission, will be estimated for the secondary endpoint of death.

A per-protocol analysis and a sensitivity analysis will be performed for the primary endpoint. The following patients will be excluded from the per-protocol analysis:Patients who do not have at least one ROTEM®/TEG®/CCT test performed *and*
Who die within 60 min after baseline blood sampling *or*
Who achieve haemostasis within 60 min of baseline sampling

Both ROTEM®-guided and TEG®-guided therapy together (i.e. the VHA arm) will be compared with the CCT arm. Separate analyses will be performed for ROTEM®-guided and TEG®-guided therapy alone for primary endpoints and correction of coagulopathy.

All applied tests will be two-sided and *p* values of 0.05 will be accepted as statistically significant. We will report *p* values with and without correction for multiple testing.

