#### Sensitivity analyses

Missing data are not expected for the primary outcome. Sensitivity analysis for secondary outcomes will be assessed using 100 multiple imputations for missing data. Rubin rules will be used to summarise the results of the multiple imputations.

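### Withdrawing patients after unblinded randomisation and replacing them conflicts in substance with the stated intention-to-treat analysis

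*Protocol article*

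**What the plan says.** All references are to the protocol article.

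- **Subject withdrawal** lists reasons why a patient may be withdrawn. For ineligibility the wording is firm: "if a patient is deemed to not meet one or more of the inclusion/exclusion criteria in retrospect they will be withdrawn". A major deviation by the subject, seen or merely suspected by the investigator, is a further possible reason. So is the investigator's judgement that continuing would endanger the patient.
- **Data collection and follow-up for withdrawn subjects** promises safety assessments to day 28. It does not mention the 24 h red cell count.
- **Subject replacement** is one sentence, with no limit by reason: "Subjects who withdraw from the study will be replaced".
- **Randomisation procedure** leaves clinical staff and site investigators unblinded.
- **Method of analysis** sets the population: "All primary and secondary outcomes will be analysed as intention-to-treat, and will include all randomised patients for whom the primary outcome" is recorded.
- **Sample size** builds in a margin: "One hundred and ninety-six patients per study arm allows a 13% dropout rate".
- **Sensitivity analyses** adds: "Missing data are not expected for the primary outcome".

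**The concern.** The text supports two readings of the primary analysis set. If withdrawn patients stay in the analysis, replacing them serves little purpose. If they leave it, the analysis is not intention-to-treat. The recorded-outcome filter allows the second reading to take effect without being announced, because nothing commits sites to recording the primary endpoint after withdrawal. The same filter governs every secondary outcome.

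The second reading matters because withdrawal can be decided with the arm and the early course known. Part of eligibility is a judgement: clinical signs of haemorrhagic shock in the view of the trauma team leader. That judgement can be reopened once the bleeding has declared itself. If patients who did badly were more readily judged ineligible, or taken off for their own safety, in one arm than in the other, the groups compared would no longer be those that were randomised. Replacement would restore the numbers but not the comparability.

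A lesser point is that the margin for dropout and the replacement rule provide for the same loss. The endpoint is complete at 24 h and no missing primary data are expected, so little dropout other than withdrawal remains.

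**Working it through.** **1. The plan's own figures.** The inputs, all from Sample size, are "approximately 28% of patients will need massive transfusion or die"; "this figure will decrease to an overall proportion of 15% in the VHA group"; and "with a power of 80% and a two-sided alpha of 0.05, 170 patients per group are required".

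Pooled normal approximation, with mean proportion (0.28 + 0.15)/2 = 0.215:

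n = [1.960 × √(2 × 0.215 × 0.785) + 0.842 × √(0.28 × 0.72 + 0.15 × 0.85)]² / 0.13² = 155.6, so 156 per arm.

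With continuity correction:

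n′ = (155.6/4) × [1 + √(1 + 4/(155.6 × 0.13))]² = 170.6, so 171 against the stated 170. That reproduces the figure to within rounding.

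Inflation: 170/0.87 = 195.4, rounded up to 196 per arm and 392 in total. The margin is 196 − 170 = 26 per arm (13.3%). No sample size figure is wrong.

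**2. Double provision.** If 196 non-withdrawn patients per arm were required and every withdrawal replaced, the number randomised per arm would be 196/(1 − w):

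| Assumed withdrawal rate w | Randomised per arm | Total |
|---|---|---|
| 2% | 200 | 400 |
| 5% | 207 | 414 |
| 10% | 218 | 436 |
| 13% | 226 | 452 |

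The planned total is 392. The overlap therefore costs enrolment, not power.

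**3. Size of the possible bias.** The document gives no withdrawal rates or outcomes, so these are assumptions: true failure 28% in both arms (no effect), withdrawals in the VHA arm only, w of 196 withdrawn, and a fraction e of those being failures.

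Retained VHA failure rate = (0.28 × 196 − e × w)/(196 − w), with 0.28 × 196 = 54.88.

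| w (share) | e = 28% | e = 50% | e = 80% |
|---|---|---|---|
| 4 (2%) | 28.0%, bias 0 | 52.88/192 = 27.5%, 0.5 points | 51.68/192 = 26.9%, 1.1 points |
| 10 (5%) | 28.0%, bias 0 | 49.88/186 = 26.8%, 1.2 points | 46.88/186 = 25.2%, 2.8 points |
| 25 (13%) | 28.0%, bias 0 | 42.38/171 = 24.8%, 3.2 points | 34.88/171 = 20.4%, 7.6 points |

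The planned effect is 28 − 15 = 13 points.

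**4. False-positive rate under the same scenario.** Withdrawals are replaced so that 196 per arm are analysed, with a two-sided 5% test and normal approximation. The columns run to e = 100% to show the extreme.

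| Withdrawn from VHA arm | e = 28% | e = 50% | e = 75% | e = 100% |
|---|---|---|---|---|
| 2% | 5.0% | 5.1% | 5.5% | 6.2% |
| 5% | 5.0% | 5.8% | 8.6% | 13.7% |
| 13% | 5.0% | 11.4% | about 37% | 72.3% |

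**5. Power if everyone randomised is analysed.** Exact power for 28% against 15% is 88.6% (chi-square) or 86.2% (Fisher) at 196 per arm, and 84.0% or 80.2% at 170 per arm. As a pessimistic case, let 13% of the VHA arm stay in the analysis and gain nothing. The VHA rate is then 0.13 × 0.28 + 0.87 × 0.15 = 16.7%, and power at 196 per arm is 77.2% or 73.6%.

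**The case against.** The strongest reply is that the conflict is inferred. Nowhere does the article say that withdrawn patients leave the analysis. The one section that defines the population takes in all randomised patients with a recorded 24 h outcome, so on a literal reading a withdrawn patient with that outcome stays. The expectation of no missing primary data fits this. The reply stands as far as it goes: this is a conflict in substance, not in so many words. It does not explain what replacement is for, or why only safety follow-up is promised.

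The scope for selection is also narrower than a quick reading suggests. Several eligibility conditions can be checked objectively: protocol activation, first transfusion, and the 3 h and 1 h windows. There are no exclusion criteria. The text does not name who decides on retrospective ineligibility. The section opens with a commitment to retain patients. All of this lowers the likely frequency but does not close the route.

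Three stronger inferences are not supported:

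- **That all deviators are removed.** Deviation by the subject is only a possible reason for withdrawal, and staff departures from the algorithm are not listed.
- **That the primary set becomes the per-protocol set.** Method of analysis defines a separate per-protocol analysis by other rules (no test performed, early death or early haemostasis), and neither ineligibility nor deviation is among them.
- **That replacement contradicts the 13% allowance.** It duplicates it, and the arithmetic holds.

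**Conclusion.** The point holds as an unresolved conflict that should be fixed. Mandatory withdrawal for ineligibility found later, discretionary withdrawal by unblinded investigators, safety-only follow-up, unlimited replacement and a recorded-outcome filter together allow randomised patients to leave an analysis that is called intention-to-treat.

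The size depends on assumptions outside the document. At 2 to 5% one-sided withdrawal with 50 to 80% failures, the spurious benefit is about 0.5 to 2.8 points. The 3.2 to 7.6 point range needs the whole dropout allowance to fall in the VHA arm alone and should not be read as a forecast. Withdrawals that are unrelated to outcome cause no bias, but the procedure cannot guarantee that.

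A reader might also infer that the trial is underpowered. The figures do not support this. With all 196 per arm analysed, power exceeds 80% at the planned effect. It falls to about 77% or 74% only if every retained VHA withdrawal, at the full 13%, gains nothing.

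**What to change.** Change the wording as follows:

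1. State that withdrawal, ineligibility found later or deviation ends study procedures but not inclusion in the primary analysis, and that all randomised patients are analysed in their allocated arm.
2. Extend the follow-up of withdrawn patients to 24 h vital status and red cell count, where consent allows.
3. Delete Subject replacement, or limit it to patients whose data may not be used.
4. Keep 392 as the number randomised, and say what the 13% covers.

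This needs no extra patients. The cost is that a few ineligible patients remain in the primary set and may dilute the effect slightly.
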